## Methods

### Recruitment

At least 140 children aged 5–18 with a diagnosis of ADHD and any accompanying co-morbidities are recruited to an observational cohort and their consent to participate in the cohort is sought by completion of a questionnaire with embedded consent to be contacted again. Their outcomes of interest are measured at recruitment (baseline) and every 6 months, via these questionnaires, which are completed by carers and blinded teachers. Carers of children with ADHD were involved in the selection of items for, design and pilot testing of the questionnaire, advised about recruitment and sat on the steering committee.

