### Randomisation

After recruitment to the STAR cohort, a three-armed internal pilot trial is subsequently conducted whereby random selections of eligible children are offered either adjunctive treatment by homoeopaths (arm 1) or nutritional therapists (arm 2). Randomisation is computer generated by an independent statistician from the University of Sheffield and held in the locked drawer of a different statistician from the University of Sheffield. Stratifying factors are age (primary 5–11/secondary 12–18), medication status (yes/no) and ADHD severity (Conners global ADHD *T* score 80+/under 80) [47]. Participants fulfilling inclusion and exclusion criteria who consent to be contacted again are identified on recruitment to the cohort. Stratifying factors are extracted and emailed to the statistician holding the randomisation list, who randomly assigns them to one of the three groups and gives them a randomly generated three-digit code by which they are subsequently identified.

Carer and child’s consent to try treatments is sought at this stage. They are sent a letter of invitation for 1 year of treatment, which includes a statement that participants can withdraw at any time; a brief description of the treatment; requests the carer to ask their child if they are happy to participate; a consent form to treatment to be signed by carer and child and returned in a pre-paid envelope; and an email address and telephone number as an alternate means of contact. The PI then rings the participants up and asks if they have any questions; if they wish to participate (if their form has not yet been returned); and if they both consent, to their details being passed on to the therapist. In the absence of a returned ‘consent to treatment’ form, carer and child’s wish to participate on the telephone is taken as verbal consent. Consent forms are then signed at the first appointment with the therapist, who further explains what treatment will constitute, as befits usual practice. Appropriate marks by young children are taken as signatures. Those children not selected act as a treatment as usual control (arm 3).

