### Inclusion/exclusion criteria

Inclusion criteria for the STAR cohort are children aged 5–18 (inclusive) with a carer-reported diagnosis of ADHD (date, venue and diagnosing physician) and a carer-reported Conners Global Index (CGI) *T* score of at least 55 (denoting mild atypicality (Table 1). Inclusion criteria for the trial are a carer-reported CGI score of at least 65 (indicating a significant problem) (Table 1).

**Table 1 Tab1:** Interpretive guideline for Conners’ *T* scores and percentiles

*T* score	Percentile	Guideline
70+	98+	Markedly atypical (significant problem)
66–70	95–98	Moderately atypical (significant problem)
61–65	86–94	Mildly atypical (possible problem)
56–60	74–85	Slightly atypical (borderline)
< 30–55	< 2–73	Average (typical: should not raise concern)

Exclusion criteria to both cohort and trial are children below the age of 5 or adults over 18; children with terminal, severe, life-limiting conditions; and families where English is not written or spoken (as the project does not have funds to provide a translation service). Exclusion criteria to the trial are children currently receiving treatment by a homoeopath or a nutritional therapist and children with CGI *T* scores below 65.

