### Outcomes

#### Patient-centred outcomes

The primary outcome measured is ADHD symptomatology measured using CGI, consisting of a 10-item total score and two sub-scores measuring restlessness/impulsivity (7 items) and emotional lability (3 items). The outcome is reported by carers (unblinded) and teachers (blinded), and each intervention is compared to usual care. Secondary outcomes are carer proxy health-related quality of life (CHU-9) and sleep. Resource use is collected by asking about medication use; further ADHD interventions being used; hospital, GP, social worker and police attendances; levels of absenteeism, exclusion and criminality; and teaching assistant and other help in school.

Resource use data is collected to enable an economic evaluation alongside a clinical trial. Evaluation will include health-related quality of life assessment, with utility measures based on the CHU-9D, the cost of consultations, medications, remedies, supplements and room hire, to enable QALY and ICER calculation. The time horizon is 1 year, during which time resource use will be collected from therapists, who complete therapist forms at each consultation documenting the time spent, the venue, medications or supplements given.

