#### Feasibility outcomes (Table 2)

Key feasibility criteria are the ability to recruit a cohort and to recruit to the interventions within the stated time frame of 2 years, by measuring recruitment rates and time taken. Numbers recruited in 2 years will be extrapolated to estimate the time needed to recruit to a full trial, and longer than 4 years will not be considered feasible. The feasibility of recruiting a representative cohort will document ADHD severity, number and type of co-morbidities, medications taken, resource usage, levels of exclusion, and criminality, and recruiting from nationally funded ADHD facilities such as special schools, secure units, NHS facilities and support services.

**Table 2 Tab2:** Feasibility criteria

Criteria	Measurement	Criteria for continuation to a full trial
Recruitment to cohort rates	Number recruited in 2 years	% recruited/sample size estimation. Minimum acceptable to proceed to a full-scale trial will consider the number of years needed to recruit the required sample size. Numbers recruited in 2 years will be extrapolated to determine how long a full trial would need to be. The required sample size will be divided by the percentage recruited in 2 years. Duration of the full trial of more than 4 years will not be considered feasible.
Recruitment to treatment rates	Percentage accepting offer	At least 30%. The percentage of participants refusing treatment will be considered to determine acceptable levels of refusal. Too many treatment refusers may lead to a high chance of a type II error and inadequate information to estimate critical parameters for a full trial with reasonable precision.
Treatment effects (statistical significance)	Standard mean difference (SMD) CGI	Mean = < .3. Since neither intervention has been tested in this form previously, estimation of the effect size cannot consider previous estimates. Since we need to know that therapies show some evidence of being helpful, a SMD of 0.3 in those implementing the therapies will be considered sufficient to proceed to full trial.
Treatment effects (clinical significance)	CGI *T* score	5 percentiles. A *T* score change of 5 percentiles is considered clinically significant, since the child has moved from one level of severity to another according to Conners (2009) [47].
Attrition: cohort	Number of PQs returned at 6 months	At least 30%
Attrition: consultations	Number of consultations attended	Adjustment of intervention provision

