#### Statistical analysis

Statistical testing is exploratory since the study is not powered to detect statistical differences. It will be used to ensure that a difference can be seen from the interventions to proceed to the full trial, to inform sample size calculation, and to pilot test the statistical analyses selected. Analysis will focus on confidence interval estimation rather than hypothesis testing. IBM SPSS 21 statistical software [56] will be used. All statistical exploratory tests will be two-tailed with significance level (alpha) set to 5%, and 95% confidence intervals presented. Outcomes will be measured by parents and teachers at baseline, 6 months and 1 year. Both interventions tested will be compared with treatment as usual with parent and teacher measurements reported.

Missing data: post hoc tests will be performed to identify any differences between groups regarding whether data is missing completely at random or not at random. 6-month missing data will be imputed using Last Observation Carried Forward or mean substitution (for baseline data) according to tool developer recommendations [47].

‘Intention to Treat’ (ITT) analysis is used whereby participants offered treatment remain within the treatment group regardless of whether they take up the offer of treatment. The method used for statistical analysis of the outcome data will be regression analysis, with outcome change score as the dependent variable and group (homoeopathic treatment or nutritional therapy, analysed separately) as the independent variable. Analysis will control for the effects of gender, ADHD severity (CGI baseline score) and age.

The acceptability of the offer of treatment will be reported by presenting numbers for all patients offered treatment. Statistical tests will be carried out to identify characteristics of those who did and did not accept and receive treatment. Sub group analysis will explore the effect of treatment on those accessing that treatment, those taking/not taking ADHD medication and those with co-occurring autism.

The clinical effect of treatment will be explored by calculating standardised mean differences [57] for those offered and taking up the offer of each treatment to obtain sample size estimates.

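### The clinical-significance continuation criterion in Table 2 is worded as a child's own CGI change and is not tied to the planned comparison with treatment as usual

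*Protocol article*

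**What the plan says.** All references are to the protocol article.

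- **Feasibility outcomes, Table 2, Treatment effects (clinical significance).** The measurement is the CGI T score and the threshold is 5 percentiles. A change of that size "is considered clinically significant, since the child has moved from one level of severity to another according to Conners (2009"). The row names no comparator, rater or time point. It does not say whether an arm mean or a share of children is meant.
- **Table 2, the row above (statistical significance).** This uses a standardised mean difference: "a SMD of 0.3 in those implementing the therapies will be considered sufficient to proceed to full trial".
- **Inclusion/exclusion criteria.** "Inclusion criteria for the trial are a carer-reported CGI score of at least 65 (indicating a significant problem").
- **Recruitment.** "Their outcomes of interest are measured at recruitment (baseline) and every 6 months".
- **Randomisation.** "Participants fulfilling inclusion and exclusion criteria who consent to be contacted again are identified on recruitment to the cohort".
- **Patient-centred outcomes.** "The outcome is reported by carers (unblinded) and teachers (blinded), and each intervention is compared to usual care".
- **Statistical analysis.** "Both interventions tested will be compared with treatment as usual with parent and teacher measurements reported". The model regresses change score on group, with adjustment for baseline CGI, gender and age, under intention to treat.

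**The concern.** The row is headed as a treatment effect, but what it describes is a child moving down a severity band. A child can do that without any treatment effect, in two ways.

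1. **Shared improvement.** Maturation, usual care, medication changes and other interventions affect every arm. The Discussion itself expects participants to try other interventions and to change medication. A contrast with TAU removes such drift on average; an uncontrolled change counts all of it.
2. **Regression to the mean.** For the carer CGI, eligibility is judged at recruitment, which is also when baseline is measured. The change therefore starts from a score that had to be at least 65 to qualify.

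The protocol already has a randomised TAU arm and a baseline-adjusted regression that deal with both, but the go rule is not attached to them. At stake is one of the criteria for taking an intervention into a full trial. This is separate from the mismatch between percentiles and T points in the same row: correcting the unit would leave the rule without a comparator.

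**Working it through.** **The plan's own figure.** The 5-percentile threshold comes with no derivation, so there is nothing to reproduce. In Table 1 the bands 56–60, 61–65 and 66–70 are each five T points wide, so the check reads the 5 as T points. The literal percentile reading follows at the end.

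**Inputs from the article.** Entry at carer CGI T of at least 65; carer baseline is the entry score; at least 30 per arm.

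**Assumptions, because the article gives no figure.** Source-population mean T 70, 75 or 80; SD 10 or 12; test-retest correlation r from 0.6 to 0.9; T rounded and capped at 90; zero treatment effect; shared improvement s of 0, 3 or 5 points.

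**One case by hand** (mean 70, SD 10, r 0.7, cap ignored).

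- The mean baseline among children at or above 65 is 75.1. Mean fall from selection = (1 − r) × (75.1 − 70) = 0.3 × 5.1 = 1.53 points.
- SD of change, ignoring its reduction by selection = 10 × √(2 × 0.3) = 7.75. SE of one arm's mean change = 7.75/√30 = 1.41.
- With s = 3 and no regression to the mean, P(arm mean falls by 5 or more) = 1 − Φ((5 − 3)/1.41) = 7.9%.
- With the 1.53 points added, it is 1 − Φ((5 − 3 − 1.53)/1.41) = 1 − Φ(0.33), about 37%. Simulation with the cap and the selected distribution gives about 32%.
- As a difference from TAU, SE = 7.75 × √(2/30) = 2.00, so P(difference of 5 or more) = 1 − Φ(2.5) = 0.6%. Here s cancels.

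**Whole grid, by simulation, inert therapy, 30 per arm.**

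| Shared improvement | Own-change rule: arms passing | Difference from TAU: pilots passing |
|---|---|---|
| 0 | 0–8% | at most about 2% |
| 3 points | about 0.2–58% | at most about 2% |
| 5 points | about 26–91% | at most about 2% |

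Selection alone lowers the arm mean by about 0.1–2.5 points. The top of each own-change range comes from mean 70, SD 12, r 0.6. If children are counted instead of averaged, about 13–41% fall by 5 or more T points with no treatment effect and no shared improvement.

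**Literal percentiles.** On a normal T scale (mean 50, SD 10), a fall of 5 percentiles is 3.1 T points from T 65 and 13.7 from T 80. With a 5-point shared improvement, an inert arm then passes in about 24–91% of pilots at source mean 70, but in only 0–14% at source mean 80.

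**The case against.** A reader might infer that the plan has adopted an uncontrolled before-and-after criterion and excluded TAU from it. The documents do not support that. The row is silent on the comparator. It sits under treatment effects and uses the primary outcome, which is compared with usual care elsewhere in the article. Its phrase about T-score change also fits the planned change-score regression. The severity-band clause may justify only the size of the threshold, since a minimal important difference is often anchored within patients and then applied between arms. This stands, and it limits the point to a rule that is not tied to the right contrast.

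A reader might also infer that regression to the mean is the main problem. It is not: alone it moves an arm mean by at most about 2.5 of the 5 points. Nor does the entry-score argument reach the blinded teacher CGI, which is not used for entry. The large pass rates need a shared improvement of 3 to 5 points, for which the article gives no figure, and they depend on how 5 percentiles is read. The child-level shares map to no decision, because the row sets no required proportion of children. All of this stands.

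It could also be said that a condensed article leaves such detail to a fuller document. That carries less weight here. The article itself fixes the threshold, its rationale and its role as a continuation criterion, and the rationale it gives is own-change.

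Finally, passing this row does not by itself send an inert therapy forward. Continuation depends on the feasibility criteria together, on reviewers' comments and on funding, and the testing is described as exploratory.

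**Conclusion.** The concern holds in limited form. The clinical-significance row is worded as own-change, names no comparator and is not linked to the adjusted TAU contrast planned for the same outcome. Followed as worded, it credits improvement shared with TAU to the therapy and, for the carer CGI, adds some regression to the mean. Shared improvement is the larger risk.

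How much this matters cannot be settled from the article. Under the assumptions above it ranges from negligible (no shared improvement and high reliability) to an inert arm passing more often than not (5 points shared with a lower source mean). A difference from TAU stays at about 2% or below throughout. The row should be corrected, but the defect does not invalidate the pilot or its planned regression.

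**What to change.** In the clinical-significance row of Table 2, state that the criterion is read, for each therapy, on the intention-to-treat difference in CGI T-score change, offer group minus TAU. Adjust it for baseline CGI and take it with its 95% CI from the regression in Statistical analysis. If a responder form is preferred, use the difference between offer group and TAU in the proportion of children improving by the stated amount. Name the rater (carer or teacher) and the time point. Report within-arm change descriptively only. Reconcile the unit of the threshold with Table 1 in the same edit.

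The cost is a sentence or two in Table 2, with no new data and no new model. The downside is that the criterion becomes harder to meet and carries two-arm sampling error: with equal arms the SE is about √2 = 1.4 times that of a single arm's change. That is the uncertainty of a treatment effect at this sample size.

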#### Statistical analysis

Statistical testing is exploratory since the study is not powered to detect statistical differences. It will be used to ensure that a difference can be seen from the interventions to proceed to the full trial, to inform sample size calculation, and to pilot test the statistical analyses selected. Analysis will focus on confidence interval estimation rather than hypothesis testing. IBM SPSS 21 statistical software [56] will be used. All statistical exploratory tests will be two-tailed with significance level (alpha) set to 5%, and 95% confidence intervals presented. Outcomes will be measured by parents and teachers at baseline, 6 months and 1 year. Both interventions tested will be compared with treatment as usual with parent and teacher measurements reported.

Missing data: post hoc tests will be performed to identify any differences between groups regarding whether data is missing completely at random or not at random. 6-month missing data will be imputed using Last Observation Carried Forward or mean substitution (for baseline data) according to tool developer recommendations [47].

‘Intention to Treat’ (ITT) analysis is used whereby participants offered treatment remain within the treatment group regardless of whether they take up the offer of treatment. The method used for statistical analysis of the outcome data will be regression analysis, with outcome change score as the dependent variable and group (homoeopathic treatment or nutritional therapy, analysed separately) as the independent variable. Analysis will control for the effects of gender, ADHD severity (CGI baseline score) and age.

The acceptability of the offer of treatment will be reported by presenting numbers for all patients offered treatment. Statistical tests will be carried out to identify characteristics of those who did and did not accept and receive treatment. Sub group analysis will explore the effect of treatment on those accessing that treatment, those taking/not taking ADHD medication and those with co-occurring autism.

The clinical effect of treatment will be explored by calculating standardised mean differences [57] for those offered and taking up the offer of each treatment to obtain sample size estimates.

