### Sample size

Sample size for the pilot trial is calculated to recruit at least 30 participants in each arm in order to estimate the pooled standard deviation of the outcome with a reasonable degree of precision for the full trial [48, 49]. We have estimated that attrition will be 20% based on a preliminary feasibility-controlled case series [50] and that a further 20% joining the STAR cohort will either not meet the first trial inclusion criteria or not accept the offer of treatment.

Sample size for the full trial will be based upon results obtained in the pilot. The calculation will be based upon the obtained effect size (SMD) for the primary outcome, significance (alpha error) of 0.05 and power of 80% and adjusted according to the levels of attrition observed. If an effect size of .4 is obtained in the pilot, then the outcomes of approximately 100 participants per group will be required. If estimated attrition of 40% is correct, then 166 participants per group will need to be recruited to the cohort.

Participants are recruited from registered charities, schools, word of mouth and support groups. The majority of participants are recruited from the city of Sheffield; however, participants are also recruited nationally and the feasibility of on-line treatments assessed.

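### The Statistical analysis section ties progression to statistical testing in a study it calls unpowered, which conflicts with its own estimation focus and with Table 2's SMD rule of 0.3

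*Protocol article*

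**What the plan says.** All references are to the protocol article.

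- **Statistical analysis, first paragraph.** It opens with "Statistical testing is exploratory since the study is not powered to detect statistical differences". The next sentence, whose subject is still statistical testing, reads "It will be used to ensure that a difference can be seen from the interventions to proceed to the full trial", and goes on to name two further uses: informing the sample size and piloting the analyses. Then comes "Analysis will focus on confidence interval estimation rather than hypothesis testing". The level is fixed as follows: "All statistical exploratory tests will be two-tailed with significance level (alpha) set to 5%, and 95% confidence intervals presented".
- **Feasibility outcomes, Table 2.** The first treatment-effect row carries the words statistical significance in its label. Its measure is the SMD on the Conners Global Index, and its rule is that "a SMD of 0.3 in those implementing the therapies will be considered sufficient to proceed to full trial".
- **Sample size.** The pilot's target is given as: "Sample size for the pilot trial is calculated to recruit at least 30 participants in each arm in order to estimate the pooled standard deviation". An SMD of 0.4 is the worked example for the full trial.
- **Discussion.** Continuation to the full trial depends on the feasibility criteria being met.

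**The concern.** Within a few sentences the section says that the study cannot support significance tests, gives those tests a part in the decision to proceed, and says that the emphasis is on estimation instead. A reader who turns to Table 2 to settle the matter finds a row labelled as significance that contains an effect-size threshold. The label supports the testing reading and the content supports the estimation reading.

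Because the Discussion makes Table 2 part of the go/no-go decision, this is more than untidy wording. If both readings remain available once the data are in, the team could choose between a stricter and a more lenient rule after seeing the result. At this sample size the two rules are far apart.

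**Working it through.** **Inputs.** Two-sided alpha 0.05 (Statistical analysis); at least 30 per arm (Sample size); SMD threshold 0.3 (Table 2); planning SMD 0.4 (Sample size). Assumptions: SD of 1, because effects are on the SMD scale; equal arms; one intervention compared with usual treatment.

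**1. The plan's own figures.** For SMD 0.4 and 80% power, n = 2(1.96 + 0.842)²/0.4² = 98.1, that is 99 per group; the t-based solution is 99.1. The article's figure of about 100 is reproduced. With 40% attrition, 100/0.6 = 166.7, against the stated 166. The effect-size scale is therefore being read as the authors use it.

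**2. What a 5% test would require in the pilot.** The standard error of an SMD is about √(2/30) = 0.258. The smallest significant observed SMD is t(0.975, 58) × 0.258 = 2.002 × 0.258 = 0.517. An observed SMD of 0.3 gives t = 0.3/0.258 = 1.16 and p = 0.25. An observed 0.4 gives t = 1.55 and p = 0.13.

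**3. Power if the sentence were applied as a 5% test.** Noncentral t, 30 per arm, no covariates:

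| True SMD | Power |
|---|---|
| 0.3 | 21% |
| 0.4 | 33% |
| 0.5 | 48% |

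The planned regression controls for baseline score, age and gender. The article gives no baseline-outcome correlation ρ, so it has to be assumed. The standard error is multiplied by √(1 − ρ²). For a true SMD of 0.4:

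| Assumed ρ | Noncentral t | Normal approximation |
|---|---|---|
| 0.5 | 42% | 43% |
| 0.7 | 57% | 58% |

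**4. The Table 2 rule on the same footing.** P(observed SMD ≥ 0.3), normal approximation with standard error 0.258:

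- True SMD 0.4: Φ((0.4 − 0.3)/0.258) = Φ(0.387) = 65% pass, 35% fail.
- True SMD 0: 1 − Φ(0.3/0.258) = 1 − Φ(1.162) = 12% pass.

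These figures are approximate. Table 2 applies its SMD to those implementing the therapy, who may number fewer than 30.

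**5. Comparison.** For a therapy at the protocol's own planning value, the chance of going forward is about 33% under an unadjusted test, about 42% to 58% under an adjusted test, and about 65% under the SMD rule.

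**The case against.** The strongest reply is that the article contains no significance gate. No section makes p<0.05 a condition for proceeding. The 5% level is a general reporting convention for exploratory tests and is paired with 95% confidence intervals. The one numerical effect rule is the SMD of 0.3, and calling it sufficient is hard to square with a second, stricter hurdle. On this view the sentence in the Statistical analysis section is loose wording, to be read through Table 2.

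Much of that stands, and it rules out several stronger readings that a reader might infer:

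- **That non-significance will be taken to mean no effect.** The article does not say so. It warns about type II error where many participants refuse treatment.
- **That a useful therapy would be dropped two times in three.** This holds only for an unadjusted 5% test at 30 per arm and a true SMD of 0.4. Under the stated SMD rule about 35% would be missed.
- **That attrition cuts the arms to 24.** The Recruitment section seeks at least 140 children. With the two 20% losses in the Sample size section, 140 × 0.8 × 0.8 = 89.6, or about 30 per arm. So 30 already appears to be net of losses, although the article does not spell this out.
- **That one can calculate how often the two rules would disagree.** The main regression is by intention to treat, while the Table 2 SMD concerns those implementing therapy. They are different estimates on different numbers of children.
- **That a significant worsening could count as a difference.** Table 2 asks for evidence that the therapies are helpful, which fixes the direction.

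The reply does not remove the grammar of the sentence, which makes statistical testing the means of deciding whether to proceed, or the Table 2 label, which points the same way.

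**Conclusion.** The concern holds as an internal contradiction about what decides progression. The Statistical analysis section gives testing a role that its own statements on power and estimation disown, and Table 2 puts a significance label on an effect-size rule. The article does not state a 5% gate, so every power figure here is conditional on the sentence being applied as one.

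On that condition, with 30 per arm and a true SMD of 0.4, the choice of rule moves the chance of proceeding from about 33% unadjusted (about 42% to 58% adjusted, at an assumed correlation of 0.5 to 0.7) to about 65%. An observed SMD between 0.3 and about 0.52 would satisfy the threshold and fail an unadjusted test if both were applied to the same comparison. That is enough to justify settling the rule before the data are examined.

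**What to change.** Three wording changes:

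1. In the Statistical analysis section, delete the clause that makes statistical testing a means of deciding whether to proceed. Its other two uses, informing the sample size and piloting the analyses, can stay.
2. State that the effect criterion for continuation is the pre-stated SMD estimate in the direction of benefit, reported with its 95% confidence interval, and that no p-value enters the decision.
3. Rename the Table 2 row *Treatment effects (effect size)*.

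No new data, participants or analyses are needed. The price is that, compared with a significance gate, a therapy with no effect is somewhat more likely to go forward: about 12% at a true SMD of 0 under the SMD rule at 30 per arm. A two-sided 5% test would let through 2.5% in the direction of benefit (0.05/2). The full trial is there to resolve such cases.
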